**Discussion:**

This study builds on research highlighting the importance of responsive parenting interventions on overall child health, as well as evidence demonstrating that providing an egg daily to infants during the complementary feeding period can prevent stunted growth. The multicomponent *Grandi Byen* intervention may provide evidence of synergistic or mediating effects of an egg intervention with instruction on psychoeducational parenting and WASH on child growth and development. *Grandi Byen* presents key innovations with implications for the well-being of children living in poverty globally.

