### Study aims and hypothesized pathways

Expanding on the conceptual framework (Fig. 1) and preliminary studies across the domains of child nutrition and development, parenting, and infectious disease, the *Grandi Byen* project takes a transdisciplinary approach—spanning the biological and social sciences—to study child growth and development, while also evaluating the potential for upscaling integrated child growth and development interventions in resource-constrained settings. The project’s specific aims are to: 1) demonstrate the reproducibility of egg-based interventions in reducing childhood stunting and test its impact on development; 2) investigate the incremental benefit of *Grandi Byen* compared to egg-only and standard care groups on primary outcomes of child growth and development; 3) explore pathways of intervention impacts on child growth and development by delineating the additive and synergistic effects of biological (nutrient biomarkers, bone age, and enteric disease), psychosocial (responsive parenting, maternal mental health, cognitive stimulation), and environmental (hygiene and sanitation, diet) factors; and 4) determine whether any incremental benefits associated with *Grandi Byen* when compared to an egg only intervention and standard care are favorable relative to additional costs. Table 1 describes specific hypotheses corresponding with the study’s primary aims, aims 1 and 2.

**Table 1 Tab1:** Primary aims and study hypotheses

Primary study aims	Hypotheses
1. To demonstrate the reproducibility and feasibility of egg-based interventions in reducing childhood stunting and test its impact on development	Hypothesis 1: Linear growth will be increased by 0.30 LAZ in children receiving one egg per day compared to standard care
	Hypothesis 2: Children receiving the egg intervention will have better cognitive, motor and language development compared to standard care.
	Exploratory Question 1: Does an egg-based intervention affect social-emotional development?
2. To investigate the incremental benefit of *Grandi Byen* compared to egg only and standard care groups on primary outcomes of child growth and development.	Hypothesis 3: Children of mothers/caregivers receiving *Grandi Byen* will increase linear growth by 0.10 LAZ compared to the egg intervention.

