	Hypothesis 4: Children of mothers/caregivers receiving *Grandi Byen* will have higher scores on child cognition, language, motor, and socio-emotional development, with an effect size of 0.36 on cognition, compared to standard care and egg nutrition groups.

The first aim allows us to replicate findings from the *Lulun Project* in a new context of Haiti and extend them to determine the effect of an egg-only intervention on developmental outcomes. Eggs alone, however, do not target the other mechanisms through which poverty impacts child growth and development. The premise of this trial is that a “bundled” intervention that combines nutrition (eggs) with a parenting intervention highlighting responsive care, ASF consumption, and improved WASH practices will act in concert to synergistically improve child growth and development over and above that of an egg intervention alone. As well as targeting additional mechanisms (e.g., responsive parenting and cognitive stimulation to promote early learning), we theorize that mothers who receive reinforcement about the importance of ASF throughout the parenting intervention will be more adherent to providing the target child with one egg per day and will continue to provide their child with diverse diets incorporating affordable ASFs post-intervention, thereby sustaining expected growth and nutrition outcomes long after the intervention ends. Aim 2 will test for the additive and synergistic effects of an egg-only nutrition intervention (arm 2) and the multicomponent intervention (arm 3) compared to standard care (arm 1).

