## Methods/Design

### Overview of study design

*Grandi Byen* is a 4-year, 3-arm RCT which aims to test an integrated nutrition (one egg a day), WASH, and responsive parenting intervention on preventing child stunting and enhancing developmental outcomes. Participants will be assigned to one of the following comparison groups: 1) standard well-baby care (control); 2) nutrition intervention (one egg per day for 6 months); and 3) integrated/multicomponent *Grandi Byen* intervention (responsive parenting, nutrition, WASH + one egg per day for 6 months). This study applies an RCT design to maximize the likelihood of establishing intervention causality and to enable us to triangulate findings across multiple measures. All children in the three arms, will be followed at multiple time points from baseline to endline (12 months) on an array of measures.

Protocols for the *Grandi Byen* study have been reviewed and approved by the Bioethics Committee of the Ministry of Public Health and Population (MSPP) in Haiti (#2021-28) and the Institutional Review Board/Human Research Protection Office at Washington University in St. Louis (# 202101035). This project is funded by the Eunice Kennedy Shriver National Institute of Child Health and Development (NICHD) (R01HD098255-02) and was registered on March 5, 2021 at https://clinicaltrials.gov/ (NCT04785352).

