### Randomization

Using the website Randomization.com [65], we generated a list of randomization codes with a reproducible seed. These codes will be used to randomize the caregiver-infant pairs into one of the three study groups in a 1:1:1 ratio, with 200 dyads assigned to each study condition.

The randomization codes are set with 120 subjects randomized into eight blocks and with each block comprising 15 subjects. Within each block, each study arm is assigned five study subjects (Fig. 4). These 120 randomization codes will be used for each of the five enrollment cycles.

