#### Parenting intervention

Mothers randomized into the multicomponent *Grandi Byen* arm will simultaneously participate in the egg intervention and a psychoeducational parenting intervention conveying messages on nutrition, WASH practices, and responsive parenting. Originally developed and tested in Uganda [39], the group-based intervention was adapted and piloted in Cap-Haitien by the study team. The intervention is rooted in social learning theory and employs active and interactive learning strategies such as verbal instruction, modeling (vicarious experience), direct experience, and receiving feedback [69]. It is also based on cognitive, behavioral, and interpersonal therapeutic techniques that encourage shaping of knowledge, problem solving, practicing new behaviors and eliciting family social support [70, 71]. Messages are delivered and reinforced through a facilitated peer-group platform. The parenting intervention has 12 modules, emphasizing several key messages that emerged in our pilot work and are known to support healthy growth and development: maternal self-care, child development (stimulating play, interactive communication, and healthy families), complementary feeding with ASFs and continued breastfeeding, and household hygiene practices such as handwashing and use of soap. An adapted program manual guides each session. Table 2 details the 12 intervention modules for the *Grandi Byen* parenting program.

**Table 2 Tab2:** *Grandi Byen* parenting intervention modules

No	Title	Session summary/empirical support	Targeted mechanism
1	Parenting for strong, healthy children	Parental aspirations; challenges encountered; introduces mothers to five principles of healthy parenting covered in *Grandi Byen*: *hygiene, food, play, conversation, self-care*. **All 5 are reinforced in every session.**	Responsive parenting
2	Strong, healthy families 1	Common family stressors that can impact child development and ways to address them. Need for positive home environment to help young children to thrive; strategies to build positive mother-infant interactions.	Responsive parenting
3	Taking care of yourself	Mothers are taught to identify and link their emotions and behaviors. Positive strategies to deal with negative emotions are introduced.	

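### The text says Aim 2 will test additive and synergistic effects, but no arm receives the parenting package without eggs, so only the incremental and total contrasts of Table 1 can be estimated

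*Protocol article*

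**What the plan says.** The section on study aims and hypothesized pathways describes Aim 2, one of the two primary aims, in two ways.

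- Table 1 words it as the incremental benefit of the multicomponent programme over eggs alone and over standard care. Hypothesis 3 is that children in arm 3 "will increase linear growth by 0.10 LAZ compared to the egg intervention". Hypothesis 4 compares arm 3 with both other arms on development, with an effect size of 0.36 on cognition.
- The text after the table goes further: "Aim 2 will test for the additive and synergistic effects of an egg-only nutrition intervention (arm 2) and the multicomponent intervention (arm 3") are to be tested against arm 1. Its stated premise is that the bundled components "will act in concert to synergistically improve child growth and development over and above that of an egg intervention alone".

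The discussion part of the abstract says, with a hedge, that the multicomponent "intervention may provide evidence of synergistic or mediating effects of an egg intervention" combined with parenting and WASH instruction.

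The overview of study design lists "1) standard well-baby care (control); 2) nutrition intervention (one egg per day for 6 months") and, third, the combined intervention. The section on the parenting intervention says that mothers in the multicomponent "arm will simultaneously participate in the egg intervention and a psychoeducational parenting intervention conveying messages on nutrition, WASH practices, and responsive parenting". The randomization section says the codes will "randomize the caregiver-infant pairs into one of the three study groups in a 1:1:1 ratio, with 200 dyads assigned to each study condition". There is no fourth arm.

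**The concern.** Additive and synergistic are competing descriptions of how two interventions combine. Telling them apart requires knowing what each does alone as well as what they do together. This trial observes eggs alone and eggs with the package, but never the package alone. The text nevertheless says that a primary aim will test both.

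What is at stake is the interpretation of a positive arm 3 versus arm 2 result. It would show that adding the package to eggs helps. It would not show whether the package works better because eggs are present, or would have done the same without them. This matters most for development. The conceptual framework section cites a meta-analysis in which responsive care had 4 to 5 times the effect of nutrition on cognitive, language and motor outcomes. On the protocol's own evidence, a plain package effect is a leading explanation of any developmental gain in arm 3.

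**Working it through.** The protocol gives no figure for synergy, so there is none to reproduce. The check is one of identifiability.

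**Inputs.** The three arms and their content come from the overview of study design, the parenting intervention section and the randomization section. The LAZ differences come from Table 1: 0.30 for eggs over standard care (Hypothesis 1) and 0.10 for arm 3 over arm 2 (Hypothesis 3). The 0.36 for cognition is from Hypothesis 4.

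**Model.** Let C be the mean under standard care, E the effect of eggs alone, P the effect of the whole package alone (responsive parenting, nutrition messages and WASH), and ExP the egg-by-package interaction on the additive scale.

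| Arm | Mean | C | E | P | ExP |
|---|---|---|---|---|---|
| 1 Standard care | C | 1 | 0 | 0 | 0 |
| 2 Egg | C + E | 1 | 1 | 0 | 0 |
| 3 Egg + package | C + E + P + ExP | 1 | 1 | 1 | 1 |
| (not in the trial) Package only | C + P | 1 | 0 | 1 | 0 |

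**Contrasts available.**

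- Arm 2 − arm 1 = E
- Arm 3 − arm 2 = P + ExP
- Arm 3 − arm 1 = E + P + ExP

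**Rank.** The matrix for arms 1 to 3 has rank 3 for 4 parameters. P + ExP lies in its row space; P alone and ExP alone do not. With the package-only row added, the rank is 4 and ExP becomes estimable.

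**With the hypothesised LAZ values.** Relative to arm 1, the arm means are 0, 0.30 and 0.30 + 0.10 = 0.40. Synergy is

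ExP = m(egg + package) − m(egg) − m(package) + m(control) = 0.40 − 0.30 − P + 0 = 0.10 − P,

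and P is never observed. These splits reproduce the same three means exactly:

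| P | ExP = 0.10 − P | Interpretation |
|---|---|---|
| 0.10 | 0 | purely additive |
| 0 | +0.10 | pure synergy |
| 0.20 | −0.10 | antagonism |

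**With the hypothesised cognition value.** Reading 0.36 as arm 3 − arm 2, ExP = 0.36 − P. P = 0.36 with no interaction fits exactly as well as P = 0 with an interaction of 0.36.

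**Can the analysis rescue it?** The planned two-level growth curve model adds repeated measurements within children. It does not add the missing combination of treatments, so the same equation holds at every time point. More children make P + ExP more precise but do not split it.

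**What a test of interaction would need (illustration only).** Assume a fourth, package-only arm, one endpoint with SD 1, alpha 0.05 and 80% power. The smallest detectable interaction is (z for alpha + z for power) × √(4/n):

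| n per arm | One-sided | Two-sided |
|---|---|---|
| 200 | 0.35 SD | 0.40 SD |
| 150 (600 in total) | 0.41 SD | 0.46 SD |

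**The case against.** The strongest reply is that nothing in the planned testing uses synergy. Table 1 already words Aim 2 as incremental benefit, and the primary model is tied to the hypotheses there. The cost-effectiveness comparisons are arm 2 versus arm 1 and arm 3 versus arm 2. The protocol never defines synergy as a factorial interaction, so the word may simply mean that the bundle beats eggs alone. All of this stands, and it limits the point to wording. It does not remove it: the sentence names additive and synergistic effects as things to be tested, and if only the increment is meant, Table 1 already says so.

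A second reply is that the protocol puts its emphasis on the bundle. That passage sets aside which element inside the package, psychosocial or hygiene, did most. It does not withdraw the claim about eggs and the package together.

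A third is that a mechanism is given: reinforcement in the parenting sessions should improve adherence to the daily egg, and egg consumption is logged in both egg arms. Comparing those logs is informative about one route, but it does not identify ExP.

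A fourth is that P could be taken as close to zero. For linear growth there is some support, since the cited meta-analysis found limited effects of responsive care on it, so the LAZ split with P = 0.20 is an algebraic illustration, not a likely scenario. For development the same source points the other way. The protocol states no such assumption for either outcome.

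A reader might also infer that the word should go from Aim 3, which speaks of "delineating the additive and synergistic effects of biological", psychosocial and environmental factors. The documents do not support that. Those are measured mediators that vary within arms, the aim is exploratory, and the rank argument does not apply to them. The usual caution about non-randomised mediators does.

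**Conclusion.** The point holds for one sentence on Aim 2 and for the matching, hedged line in the abstract. The trial identifies P + ExP and not its parts, so it can test neither additivity nor synergy between eggs and the package. The shortfall is one parameter, and no sample size or model on these three arms makes it up without an outside assumption about P. This follows from the arm structure alone, with synergy taken as departure from additivity of the two effects.

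A reader might go further and conclude that Aim 2 as a whole cannot be answered, or that synergy will be claimed from the results. The documents support neither. Hypotheses 3 and 4 are contrasts that the randomised arms can estimate. The only forward-looking statement about synergy findings is the abstract's, which says the trial may provide such evidence, and the article's main discussion section makes no synergy claim. This is a correction that should be made to the stated aim, not a flaw in the primary comparisons.

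**What to change.** Reword the Aim 2 sentence to match Table 1: the incremental effect of adding the parenting, nutrition-message and WASH package to eggs (arm 3 − arm 2), and the total effect of the combined intervention (arm 3 − arm 1). Bring the abstract line into agreement. Add one statement that the egg-by-package interaction is not estimable in this design, so a positive arm 3 versus arm 2 result will not be reported as synergy. Synergy may stay as the motivating theory if it is labelled as such.

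Leave the Aim 3 wording on mediating factors in place, as exploratory and non-randomised.

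No arm, sample size, hypothesis or analysis changes. The cost is that the claim to test synergy is given up.

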**Fig. 2 Fig2:**
[figure not shown]
Hypothesized pathways from study conditions to outcomes

The fourth aim highlights a major gap related to the effective translation and continuity of evidence-based programs in real-world settings by addressing economic considerations related to public health programming. We intentionally selected interventions (egg only and *Grandi Byen*) that are feasible for translation into programming and policy with preliminary evidence to support this [60]. Experts in implementation science recognize that there is limited research on cost-effectiveness of evidence-based interventions and emphasize that future research addresses this gap [61]. Multicomponent interventions are at risk for being expensive and complicated to reproduce in multiple contexts [62]. Moreover, costly interventions would likely not be sustainable in low-resource contexts [63]. The inclusion of an economic evaluation will allow us to determine whether any incremental benefits associated with *Grandi Byen* when compared to an egg-only intervention and standard well-baby care are favorable relative to additional costs, a question of efficiency. Given that millions of children globally living in poverty are not reaching their full developmental potential, there is a tremendous need for efficacious and cost-effective interventions to disrupt early childhood trajectories towards long-term deleterious outcomes.

## Methods/Design

### Overview of study design

*Grandi Byen* is a 4-year, 3-arm RCT which aims to test an integrated nutrition (one egg a day), WASH, and responsive parenting intervention on preventing child stunting and enhancing developmental outcomes. Participants will be assigned to one of the following comparison groups: 1) standard well-baby care (control); 2) nutrition intervention (one egg per day for 6 months); and 3) integrated/multicomponent *Grandi Byen* intervention (responsive parenting, nutrition, WASH + one egg per day for 6 months). This study applies an RCT design to maximize the likelihood of establishing intervention causality and to enable us to triangulate findings across multiple measures. All children in the three arms, will be followed at multiple time points from baseline to endline (12 months) on an array of measures.

Protocols for the *Grandi Byen* study have been reviewed and approved by the Bioethics Committee of the Ministry of Public Health and Population (MSPP) in Haiti (#2021-28) and the Institutional Review Board/Human Research Protection Office at Washington University in St. Louis (# 202101035). This project is funded by the Eunice Kennedy Shriver National Institute of Child Health and Development (NICHD) (R01HD098255-02) and was registered on March 5, 2021 at https://clinicaltrials.gov/ (NCT04785352).

### Sample size

The study sample will comprise 600 mother-infant dyads, with 200 eligible pairs each assigned to one of the three study conditions. Using the software Optimal Design (Version 3.01) [64], we determined that a sample of 600 participants will lend our study adequate statistical power which allows us to observe an effect from the study interventions. Using the repeated measures module of the software under the setting of a cluster randomized trial with person-level outcomes and assuming an intraclass correlation coefficient (ICC) of 0.7, we found that the study will have a statistical power of 0.80 to detect an effect size of 0.338, which is slightly above the small effect size defined by Cohen’s d. The ICC of 0.7 is typical for individual’s serial correlation found from most longitudinal studies. If the ICC is reduced to 0.3, the study can detect an even smaller effect size of 0.31.

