The primary analytic model to test primary hypotheses of the primary study aims—aims 1 and 2 (Table 1)—is the growth curve analysis using hierarchical linear modeling (HLM) or hierarchical generalized linear modeling (HGLM), depending on whether the outcome variable is a normally distributed continuous variable or a categorical variable. In the current study, the different timepoints (i.e., five waves of data collection at baseline and 3-, 6-, 9-, and 12-month follow-ups) are nested within children. These clustering effects violate the independent-observation assumption embedded in a linear model, so we will use HLM (also known as a random-effect or mixed-effect model) to control for the nesting structure of the data. In this study sample, there is only one child per parent, thus the nesting effect of children within families is absent. We therefore plan to treat mother-child pairs as one study level. However, we apply a two-level HLM model that treats time as level 1 and children as level 2.

Aim 3 examines the pathways to child growth and development by testing a series of mediational effects of secondary outcomes: responsive parenting, child dietary diversity and nutrient intakes, biomarker status, allergies, bone maturation, acute diarrhea, and respiratory morbidity. To conduct HLM or HGLM analysis for this aim, we will employ the multilevel analysis specially developed for testing mediational effects [89]. The analysis will involve three models: a full model, a reduced model, and a model using the mediator as a dependent variable. For the time-to-event outcomes (diarrhea episode, respiratory infections, and allergies in first 6 months of follow-up), we will use a proportional hazards model [90, 91].

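### The claim of adequate power does not cover primary Hypothesis 3 (0.10 LAZ), and the detectable effects of 0.338 and 0.31 cannot be reproduced from the disclosed design

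*Protocol article*

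**What the plan says.** The Sample size section has "200 eligible pairs each assigned to one of the three study conditions" and concludes that power is adequate: "we found that the study will have a statistical power of 0.80 to detect an effect size of 0.338". The calculation was run in a repeated-measures power module "under the setting of a cluster randomized trial with person-level outcomes and assuming an intraclass correlation coefficient (ICC) of 0.7", and the ICC is justified as serial correlation within an individual. A second figure follows: "If the ICC is reduced to 0.3, the study can detect an even smaller effect size of 0.31".

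The Randomization section allocates individuals; the codes "randomize the caregiver-infant pairs into one of the three study groups in a 1:1:1 ratio".

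Table 1 (Study aims and hypothesized pathways) lists the hypotheses under the two primary aims:
- Hypothesis 1: "Linear growth will be increased by 0.30 LAZ in children receiving one egg per day compared to standard care".
- Hypothesis 3: children in the Grandi Byen arm "will increase linear growth by 0.10 LAZ compared to the egg intervention".
- Hypothesis 4: an effect size of 0.36 on cognition.

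The Statistical analyses section treats the hypotheses of Aims 1 and 2 as primary. It tests them one-sided with a two-level growth curve (time within child) over five waves. The Sample size section does not mention 0.10 LAZ and gives no alpha, LAZ SD or number of waves.

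**The concern.** One general statement of adequate power stands for all primary hypotheses, yet the smallest target is far below the effect the study is said to detect. Hypothesis 3 carries the growth half of Aim 2, the increment of the bundled intervention over eggs alone. The same arm 3 minus arm 2 difference enters the cost-effectiveness ratio. A reader who trusts the power statement could take a non-significant Hypothesis 3 as evidence that the bundle adds nothing to growth, when the trial could well miss a true 0.10 LAZ.

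The second issue is that 0.338 and 0.31 do not follow from the design as described, so the basis of the adequacy claim cannot be checked.

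**Working it through.** **Inputs from the article:** 200 per arm, so N = 400 in a pairwise contrast; individual 1:1:1 allocation; ICC 0.7 or 0.3; five growth waves; one-sided tests; power 0.80. **Assumed:** alpha 0.05; LAZ SD 1.0 to 1.2; baseline correlation r 0.7 to 0.8. The multiplier M = z(alpha) + z(0.80) is 2.486 one-sided and 2.802 two-sided.

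**1. Reproducing 0.338 and 0.31.** With the child as the cluster and m waves, the variance of a child's mean in SD units is V = ICC + (1 − ICC)/m, and the detectable effect is M × √(4V/N).
- m = 5, ICC 0.7: V = 0.76 and √(4 × 0.76/400) = 0.0872, giving 0.244 two-sided or 0.217 one-sided.
- m = 5, ICC 0.3: V = 0.44 and the root is 0.0663, giving 0.186 or 0.165.
- m = 3 (the number of ASQ visits): 0.251/0.205 two-sided, 0.222/0.182 one-sided.
- m = 1: the root is 0.100, giving 0.280 or 0.249.

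None of these gives the stated pair. Under this time-averaged model the ratio of the two figures does not depend on alpha, power or N. The stated ratio is 0.338/0.31 = 1.09 (1.07 to 1.11 allowing for rounding). The model gives 1.00 for one wave, √(0.85/0.65) = 1.14 for two, 1.22 for three and √(0.76/0.44) = 1.31 for five. No whole number of waves fits.

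**2. Hypothesis 3 against the stated figure.** 0.10 LAZ equals 0.338 SD only if the SD is 0.10/0.338 = 0.296 LAZ, and equals 0.31 SD only if it is 0.10/0.31 = 0.323. Taking the plan's own precision, the implied one-sided standard error is 0.338/2.486 = 0.136 SD. Power is then Φ(0.10/0.136 − 1.645) = 18% at SD 1.0, and 15% at SD 1.2.

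**3. Hypothesis 3 at 200 per arm.** Power = Φ(0.10/SE − 1.645), with SE = s × √(2/200) = 0.1s.

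| Analysis | Residual SD s | One-sided power |
|---|---|---|
| Simple comparison, SD 1.0 | 1.0 | 26% |
| Simple comparison, SD 1.2 | 1.2 | 21% |
| Baseline-adjusted, r 0.8, SD 1.0 | √(1 − 0.64) = 0.60 | 51% |
| Baseline-adjusted, r 0.7, SD 1.2 | 1.2 × √(1 − 0.49) = 0.857 | 32% |
| ANCOVA, mean of four follow-ups, ICC 0.7, SD 1.0 | √(0.775 − 0.49) = 0.534 | 59% |
| Same, SD 1.2 | 0.641 | 47% |

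The last two rows assume the full 0.10 is present from month 3 and that no child is lost.

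**4. Numbers for 0.80 power.** n per arm = 2 × (2.486 × s/0.10)². Unadjusted, this is 1,237 at SD 1.0 and 1,781 at SD 1.2. Baseline-adjusted with r 0.8 and SD 1.0, it is 446. The plan has 200.

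**The case against.** **Undisclosed inputs.** The software's growth module takes quantities the article does not report, such as slope and level-1 variance. If the effect is standardised by the SD of true child slopes, a detectable effect above 0.280 is possible. A three-level setup with 200 clusters comes close (0.336/0.315), though it is not 600 individually randomised dyads. A reader might infer a proven software error; the documents support only that the pair is not reproducible from what is disclosed.

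**The cluster setting.** A reader might see a contradiction with individual randomisation. The article explains the ICC as serial correlation within a person, so the cluster is the child. The wording is loose, not contradictory.

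**The ICC direction.** A lower ICC enlarges the detectable effect for a slope under compound symmetry without slope variance. The article does not specify that structure, so this cannot be held against it.

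**Hypotheses 1 and 4.** Setting 0.30 LAZ beside 0.338 SD suggests that Hypothesis 1 is also short. But 0.338 is larger than a simple comparison needs: at 200 per arm, Hypothesis 1 has 91% one-sided power at SD 1.0 and 80% at SD 1.2. The 0.36 of Hypothesis 4 exceeds 0.338. The absence of an attrition allowance is something a condensed article may leave to the full protocol.

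**How badly Hypothesis 3 fares.** It would be too strong to say that it will most likely be non-significant if true. With one-sided testing and repeated follow-ups, the most favourable case under the plan's ICCs is 59%, somewhat better than even.

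None of this brings Hypothesis 3 to 0.80. That would take assumptions outside the plan's ICCs: at ICC 0.9, ANCOVA on four follow-ups reaches 90% at SD 1.0.

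**Conclusion.** The statement of adequate power is wrong as it stands for Hypothesis 3. Power for 0.10 LAZ is 21-26% for a simple comparison, 32-51% with baseline adjustment and at best 47-59% with four averaged follow-ups. These figures rest on an assumed one-sided alpha of 0.05 and LAZ SD of 1.0 to 1.2, but the conclusion is not sensitive to them: at SD 0.8 a simple comparison has 35%, and at SD 0.5 still only 64%.

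The non-reproducible 0.338/0.31 pair is the lesser issue. It errs on the conservative side for Hypotheses 1 and 4 and may have an explanation in inputs that are not reported.

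**What to change.** - Recompute the detectable effect for three individually randomised arms under the planned model, stating alpha, SD, number of waves and the contrast tested.
- Restate power separately for each primary hypothesis in Table 1.
- State that Hypothesis 3 at 0.10 LAZ is not powered at 0.80. Report the arm 3 minus arm 2 LAZ difference as an estimate with a 95% CI, and say in advance that non-significance will not be read as no incremental benefit. As a guide, at SD 1.1 the half-width is 1.96 × 1.1 × 0.1 = 0.22 LAZ unadjusted, or 0.13 with baseline adjustment at r 0.8. Either is wider than the target itself.

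The cost is a rewritten sample-size paragraph and a sentence in the analysis section. No extra participants are needed. The downside is that Hypothesis 3 is presented less favourably.
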